### Practitioner qualification and standardization

All acupuncture procedures will be performed by licensed acupuncturists with a minimum of five years of clinical experience in reproductive medicine. Prior to trial initiation, all practitioners will complete a standardized training session covering the precise anatomical location of each acupoint, needle manipulation techniques to achieve *de qi*, and the operation of the electroacupuncture device. Mechanistic rationale for acupoint selection: The selected acupoints are based on both TCM theory and modern research. Zhongwan (RN12), Qihai (RN6), Guanyuan (RN4), and Zhongji (RN3) are located on the Ren Meridian and are traditionally used to regulate the uterus and nourish the Chong and Ren vessels, which govern reproduction. Guilai (ST29) and Shenshu (BL23) tonify the kidney and regulate menstruation. Ciliao (BL28) targets the sacral parasympathetic nerves, potentially enhancing uterine blood flow. Xuehai (SP10), Sanyinjiao (SP6), and Taixi (KI6) are used to activate blood circulation, resolve stasis, and balance endocrine function.

### Outcomes

#### Primary outcomes

The primary outcome is embryo implantation rate, defined as the number of implanted embryos per transferred embryo (18).

#### Secondary outcomes

1. Clinical pregnancy rate. Presence of a gestational sac with embryonic cardiac activity confirmed by transvaginal ultrasound at 30 days post-embryo transfer (19).

2. Hormonal profiles. Serum levels of β-human chorionic gonadotropin (β-hCG), luteinizing hormone (LH), progesterone (P), and estradiol (E2) measured at 14 days post-transfer.

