### Randomization and blinding

A total of 100 eligible participants will be randomly allocated to either the experimental or control group in a 1:1 ratio using permuted block randomization. The allocation sequence will be concealed through sequentially numbered, opaque, sealed envelopes to ensure randomization integrity. This trial employs a single-blind design wherein participants will remain blinded to their group assignment throughout the trial. Practitioners administering acupuncture will necessarily be unblinded due to the inherent characteristics of the intervention. To minimize detection bias, outcome assessors (including ultrasound technicians evaluating gestational sacs and laboratory personnel analyzing hormone levels) will be strictly segregated from the acupuncture procedures and will remain blinded to group allocation. Furthermore, the statistician responsible for data analysis will also be blinded until the analysis plan is finalized and the database is locked. While performance bias cannot be entirely eliminated due to practitioner unblinding, the use of a standardized sham protocol aims to mitigate differential participant-provider interactions.

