### Procedure

All participants will receive standard Western medical treatment during their IVF-ET cycles, including ovulation induction medications in the preparatory phase and luteal phase support following embryo transfer. The administration of these foundational medications cannot be fully standardized due to interpatient variability in physiological parameters. Treatment protocols are therefore individualized based on patient characteristics to maximize pregnancy success rates. To address potential confounding, the following IVF cycle characteristics will be prospectively documented for each participant: specific controlled ovarian stimulation protocol (e.g., GnRH agonist long protocol, GnRH antagonist protocol, or others), type and dosage of gonadotropins, embryo stage at transfer (cleavage stage or blastocyst), embryo quality grade, and number of embryos transferred. Acupuncture or sham acupuncture intervention will be administered twice weekly from day 5 of the menstrual cycle until the day before embryo transfer, with a minimum requirement of three completed acupuncture sessions.

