### Sample size

Based on previously reported data, the embryo implantation rate in RIF patients receiving acupuncture combined with hormone replacement therapy (HRT) is estimated at 35.42%, compared with 20.13% in patients receiving HRT alone (21). To detect this difference with a two-sided significance level of α = 0.05 and a power of 90% (1-β = 0.90) using a 1:1 allocation ratio, a total of 358 participants (179 per group) would be required for a fully powered confirmatory randomized controlled trial (calculated using the formula for comparing two independent proportions with continuity correction).

As an exploratory clinical study designed with pragmatic considerations, we determined the sample size through comprehensive evaluation of feasibility constraints rather than formal power calculations. This pragmatic approach is consistent with the methodological guidance for pilot trials, which emphasizes that sample sizes should be based on practical considerations. The final sample of 100 participants (50 per group) has been established after accounting for anticipated recruitment challenges, 24-month study duration limitations, available research funding, and current staffing capacity. We acknowledge that with a sample size of 100, the trial may have limited statistical power to detect small-to-moderate treatment effects. Therefore, the trial is not designed or powered to produce definitive efficacy conclusions, and the results will be interpreted with appropriate caution. The findings will primarily serve to generate preliminary estimates of between-group differences in embryo implantation rate, inform formal power calculations for a subsequent large-scale, multicenter RCT, and evaluate protocol feasibility parameters including recruitment rate, retention rate, and protocol adherence.

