### Statistical analysis

Baseline characteristics will be summarized using descriptive statistics, with continuous variables reported as mean ± standard deviation or median (interquartile range) depending on data distribution, and categorical variables reported as frequencies and percentages. The following baseline characteristics will be collected and compared between groups: age, BMI, duration of infertility, number of previous failed IVF-ET cycles, basal FSH level, AMH level, AFC, endometrial thickness, and number of embryos transferred. Between-group comparisons of baseline characteristics will employ independent samples t-tests or Mann-Whitney U tests for continuous variables, and χ² tests or Fisher’s exact tests for categorical variables, as appropriate.

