Before conducting comparative analysis tests on all variables, a data normality test will be performed first to ensure the appropriateness of the selected comparative analysis methods. For the primary outcome, embryo implantation rate, the unit of analysis is defined as the individual embryo. However, because each participant may contribute multiple embryos, the data exhibit a clustered structure that violates the independence assumption of conventional statistical tests. Therefore, between-group comparisons for the primary outcome will be performed using a Generalized Estimating Equation (GEE) model with a logit link function and a binomial distribution family. An exchangeable correlation structure will be specified to account for within-patient clustering. The model will include treatment group (acupuncture vs. sham acupuncture) as the primary independent variable, and will be adjusted for the following pre-specified clinically relevant covariates: age, BMI, number of previous failed IVF-ET cycles, controlled ovarian stimulation protocol type (categorical), embryo stage (cleavage vs. blastocyst), embryo quality (good vs. fair, dichotomized for analysis), and number of embryos transferred. Results will be reported as odds ratios with 95% confidence intervals and P-values based on robust standard errors. For secondary outcomes, between-group comparisons will employ: 1) χ² or Fisher’s exact tests for dichotomous outcomes (clinical pregnancy rate); 2) independent samples t-tests or Mann-Whitney U tests for continuous variables (reproductive hormone levels). The intention-to-treat population will serve as the primary analysis set, with missing outcome data will be handled using multiple imputation by chained equations (MICE) under the assumption of missing at random (MAR), with sensitivity analyses performed under missing not at random (MNAR) assumptions to assess the robustness of the findings.

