In addition to the primary analysis, sensitivity analyses will be performed to assess the robustness of the primary outcome, including per-protocol analysis and complete-case analysis. Exploratory subgroup analyses will be conducted to generate hypotheses for future research. These analyses will evaluate the primary outcome stratified by age (25-30, 30-35, or 35–40 years), BMI categories (normal weight: 18.5≤BMI<23; overweight: 23≤BMI< 27.5; obese: BMI≥27.5) (22), and the number of acupuncture sessions received (3, 4, 5, or ≥6 sessions). Given the limited sample size of this pilot trial, these subgroup analyses are purely descriptive and will be presented without formal statistical comparisons between subgroups to avoid spurious findings. No adjustment for multiple testing will be applied, as the purpose is hypothesis generation rather than confirmatory inference. The results will be interpreted with extreme caution and will serve solely to inform the design of future larger trials. All analyses will be performed using SPSS software, with statistical significance defined as a two-tailed *P*-value <0.05.

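### β-hCG is drawn a fixed time after transfer for both embryo stages and compared without regard to stage, which costs precision mainly among pregnant women

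*Protocol article*

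**What the plan says.** Under Secondary outcomes, β-hCG, LH, progesterone and estradiol share one sampling time, "measured at 14 days post-transfer". Nothing there refers to embryo age or to the day of fertilisation.

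Under Procedure, the cycle characteristics to be documented for each woman include "embryo stage at transfer (cleavage stage or blastocyst", so both stages are expected. The stated reason for recording them is to deal with potential confounding.

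Under Statistical analysis, hormones are compared by "independent samples t-tests or Mann-Whitney U tests for continuous variables (reproductive hormone levels", with no stage term. The same section puts "embryo stage (cleavage vs. blastocyst), embryo quality (good vs. fair, dichotomized for analysis), and number of embryos transferred" among the covariates of the GEE model, but only for implantation rate.

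Randomization and blinding describes allocation "in a 1:1 ratio using permuted block randomization" and states no stratification by stage. The listed baseline comparisons are "age, BMI, duration of infertility, number of previous failed IVF-ET cycles, basal FSH level, AMH level, AFC, endometrial thickness, and number of embryos transferred"; stage is not among them.

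**The concern.** β-hCG early in pregnancy depends strongly on how old the conceptus is. A clock that starts at transfer gives a different embryo age for a cleavage-stage transfer than for a blastocyst transfer, so the two groups are read at different points on a rising curve. The plan already treats stage as prognostic for implantation. It does not use stage for the one hormone where stage also changes the effective time of measurement.

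What is at stake is the usefulness of the β-hCG estimate. The Discussion gives the hormones a mechanistic role, and the pilot exists to produce estimates rather than tests. Spread caused by mixing two embryo ages, and chance differences in stage mix between small groups of pregnancies, both degrade that estimate. The remedy uses a variable that is already collected.

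**Working it through.** The article gives no β-hCG figure (no SD, rate of rise, stage mix or power), so there is nothing to reproduce. The document supplies the sampling clock, the two stages, the test, 50 women per arm, and the anticipated implantation rates of 20.13% and 35.42% (Sample size). Everything biological below is an assumption.

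**1. Embryo age at the draw.** Assume cleavage is day 3 and blastocyst day 5. Age at the draw is 3 + 14 = 17 days or 5 + 14 = 19 days, a gap of 2 days.

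**2. Ratio between stages among pregnancies.** Ratio = 2^(gap / doubling time).

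| Assumed doubling time | Ratio | ln ratio |
|---|---|---|
| 1.4 days | 2.69 | 0.990 |
| 2.1 days | 1.94 | 0.660 |
| 3 days | 1.59 | 0.462 |

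**3. Variance inflation among pregnant women.** Inflation = 1 + f(1 − f)(ln ratio)² / SD², with blastocyst share f = 0.5 and within-stage log SD = 0.7 (SD² = 0.49).
- 1.4 days: 1 + 0.25 × 0.980 / 0.49 = 1.50
- 2.1 days: 1 + 0.25 × 0.436 / 0.49 = 1.22
- 3 days: 1 + 0.25 × 0.214 / 0.49 = 1.11

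With SD from 0.5 to 0.9, f from 10% to 50% and doubling times from 1.5 to 3 days, the factor runs from 1.02 to 1.85. It approaches 1 when one stage predominates.

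**4. Shift from a 20-point stage imbalance among pregnant women.** exp(0.2 × ln ratio) = 1.10, 1.14 and 1.22 for doubling times of 3, 2.1 and 1.4 days, with no treatment effect.

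**5. How likely that imbalance is.** Taking the implantation rates as a rough guide to pregnancies, 50 × 0.2013 ≈ 10 and 50 × 0.3542 ≈ 18 per arm. With f = 0.5 in both arms, the exact binomial chance of a gap of at least 20 points is about 50% with 10 per arm, 36% with 15 and 24% with 18. A normal approximation gives 27% for 15 per arm.

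**6. The same effect when all women are analysed.** Assume 30% pregnant, log SD 0.7 in pregnant and 0.3 in non-pregnant women, and an average pregnant to non-pregnant ratio of 20 to 100. The log-scale variance without stage is 0.3 × 0.7 × (ln 20)² + 0.3 × 0.49 + 0.7 × 0.09 = 2.09 at 20-fold, and 4.66 at 100-fold. Stage adds 0.3 × 0.25 × (ln ratio)², which is 0.016 (3 days) to 0.074 (1.4 days). The inflation is between 0.016 / 4.66 = 0.3% and 0.074 / 2.09 = 3.5%.

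**7. False-positive rate.** Simulation under no treatment effect (50 per arm, 30% pregnant, log SD 0.7, twofold stage ratio, equal expected stage shares, 4,000 runs) gave 5.0% for Mann-Whitney in all women and 5.3% for the t-test in pregnant women. The nominal level holds.

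**The case against.** The strongest reply is that the article does not specify a pregnant-only comparison. Hormones are measured without restriction to pregnancies, and intention-to-treat is the primary analysis set. In that set the split between pregnant and non-pregnant women dominates β-hCG, and stage is almost invisible (step 6). This stands, and it limits the point.

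Second, the arms are randomised, so stage mix is equal in expectation. This stands too. A reader might infer that the comparison is biased, or that a β-hCG difference could not be attributed to acupuncture at all. The document does not support that reading. Simulated error rises only if the true stage shares differ between arms (7.9% and 15.8% for the pregnant-only t-test at gaps of 20 and 40 points), and nothing in the article suggests that they do.

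Third, even among pregnant women the shift lies within sampling error. With log SD 0.7 and 10 to 18 pregnancies per arm, the standard error of the log ratio is 0.7 × √(2/10) = 0.31 to 0.7 × √(2/18) = 0.23. The shifts in step 4 (0.092 to 0.198 on the log scale) are therefore about 0.3 to 0.85 of a standard error. This is fair: the interval already covers chance imbalance. But in an estimation pilot, avoidable error of that order is still worth removing.

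Finally, adjusted secondary analyses are often left to an analysis plan. Here, though, the article itself fixes both the sampling clock and the unadjusted test, and it already names stage as a covariate elsewhere.

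**Conclusion.** The point holds as a minor precision issue. One post-transfer clock, two embryo stages and an unadjusted test are all in the text, and no section corrects for embryo age. If β-hCG is examined among pregnant women, mixing stages costs roughly 10% to 50% in log-scale variance and leaves the estimate open to chance shifts of about 10% to 22%. If all women are compared, the cost is a few per cent at most.

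These sizes rest on an assumed two-day age gap, a doubling time of 1.4 to 3 days, a log SD of 0.7 and an even stage mix. The article gives none of these, and a centre that transfers mostly one stage would see much less. Balance in expectation also assumes that acupuncture does not affect which stage is transferred.

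**What to change.** Keep the day-14 visit; the remedy belongs in the analysis. In Statistical analysis, take β-hCG out of the general hormone test and state two things:

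- The between-arm β-hCG comparison includes embryo stage, or embryo age in days at the draw, as a covariate. Neither named test can carry a covariate, so this means a regression model, or a rank test stratified by stage.
- Log β-hCG among pregnant women, adjusted for stage, is reported with its confidence interval and labelled descriptive, because pregnancy is an outcome that follows randomisation.

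The cost is one model term and two sentences. Stage is already recorded, so no new data are needed. The downside is that the pregnant-only analysis is not a randomised comparison and may carry selection effects. Adjusting for stage makes the same assumption that the primary model already makes, namely that treatment does not change the stage transferred.

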### Safety evaluation

Adverse events (e.g., needle fainting, hematoma, or drug-related adverse reactions) will be systematically documented and severity-graded in accordance with the Common Terminology Criteria for Adverse Events (CTCAE) version 5.0 (20).

### Data management

Trained researchers will record all data using standardized case report forms (CRFs). To ensure data accuracy, we will employ a dual-entry system with automated consistency validation, with any discrepancies adjudicated by the principal investigators.

### Quality control

An expert panel comprising specialists in acupuncture, obstetrics/gynecology, methodology, and biostatistics has rigorously reviewed the trial protocol. To minimize bias, we will implement centralized randomization. Prior to trial initiation, all research staff will undergo standardized training covering: 1) participant recruitment procedures, 2) randomization protocols, 3) acupuncture intervention techniques, and 4) patient communication strategies. Data will be systematically recorded using uniform CRFs, with monthly trial monitoring conducted by the research team.

### Sample size

Based on previously reported data, the embryo implantation rate in RIF patients receiving acupuncture combined with hormone replacement therapy (HRT) is estimated at 35.42%, compared with 20.13% in patients receiving HRT alone (21). To detect this difference with a two-sided significance level of α = 0.05 and a power of 90% (1-β = 0.90) using a 1:1 allocation ratio, a total of 358 participants (179 per group) would be required for a fully powered confirmatory randomized controlled trial (calculated using the formula for comparing two independent proportions with continuity correction).

As an exploratory clinical study designed with pragmatic considerations, we determined the sample size through comprehensive evaluation of feasibility constraints rather than formal power calculations. This pragmatic approach is consistent with the methodological guidance for pilot trials, which emphasizes that sample sizes should be based on practical considerations. The final sample of 100 participants (50 per group) has been established after accounting for anticipated recruitment challenges, 24-month study duration limitations, available research funding, and current staffing capacity. We acknowledge that with a sample size of 100, the trial may have limited statistical power to detect small-to-moderate treatment effects. Therefore, the trial is not designed or powered to produce definitive efficacy conclusions, and the results will be interpreted with appropriate caution. The findings will primarily serve to generate preliminary estimates of between-group differences in embryo implantation rate, inform formal power calculations for a subsequent large-scale, multicenter RCT, and evaluate protocol feasibility parameters including recruitment rate, retention rate, and protocol adherence.

### Statistical analysis

Baseline characteristics will be summarized using descriptive statistics, with continuous variables reported as mean ± standard deviation or median (interquartile range) depending on data distribution, and categorical variables reported as frequencies and percentages. The following baseline characteristics will be collected and compared between groups: age, BMI, duration of infertility, number of previous failed IVF-ET cycles, basal FSH level, AMH level, AFC, endometrial thickness, and number of embryos transferred. Between-group comparisons of baseline characteristics will employ independent samples t-tests or Mann-Whitney U tests for continuous variables, and χ² tests or Fisher’s exact tests for categorical variables, as appropriate.

Before conducting comparative analysis tests on all variables, a data normality test will be performed first to ensure the appropriateness of the selected comparative analysis methods. For the primary outcome, embryo implantation rate, the unit of analysis is defined as the individual embryo. However, because each participant may contribute multiple embryos, the data exhibit a clustered structure that violates the independence assumption of conventional statistical tests. Therefore, between-group comparisons for the primary outcome will be performed using a Generalized Estimating Equation (GEE) model with a logit link function and a binomial distribution family. An exchangeable correlation structure will be specified to account for within-patient clustering. The model will include treatment group (acupuncture vs. sham acupuncture) as the primary independent variable, and will be adjusted for the following pre-specified clinically relevant covariates: age, BMI, number of previous failed IVF-ET cycles, controlled ovarian stimulation protocol type (categorical), embryo stage (cleavage vs. blastocyst), embryo quality (good vs. fair, dichotomized for analysis), and number of embryos transferred. Results will be reported as odds ratios with 95% confidence intervals and P-values based on robust standard errors. For secondary outcomes, between-group comparisons will employ: 1) χ² or Fisher’s exact tests for dichotomous outcomes (clinical pregnancy rate); 2) independent samples t-tests or Mann-Whitney U tests for continuous variables (reproductive hormone levels). The intention-to-treat population will serve as the primary analysis set, with missing outcome data will be handled using multiple imputation by chained equations (MICE) under the assumption of missing at random (MAR), with sensitivity analyses performed under missing not at random (MNAR) assumptions to assess the robustness of the findings.

In addition to the primary analysis, sensitivity analyses will be performed to assess the robustness of the primary outcome, including per-protocol analysis and complete-case analysis. Exploratory subgroup analyses will be conducted to generate hypotheses for future research. These analyses will evaluate the primary outcome stratified by age (25-30, 30-35, or 35–40 years), BMI categories (normal weight: 18.5≤BMI<23; overweight: 23≤BMI< 27.5; obese: BMI≥27.5) (22), and the number of acupuncture sessions received (3, 4, 5, or ≥6 sessions). Given the limited sample size of this pilot trial, these subgroup analyses are purely descriptive and will be presented without formal statistical comparisons between subgroups to avoid spurious findings. No adjustment for multiple testing will be applied, as the purpose is hypothesis generation rather than confirmatory inference. The results will be interpreted with extreme caution and will serve solely to inform the design of future larger trials. All analyses will be performed using SPSS software, with statistical significance defined as a two-tailed *P*-value <0.05.

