## Abstract

**Objective:**

Repeated implantation failure (RIF) in *in vitro* fertilization-embryo transfer (IVF-ET) remains a challenging clinical issue. Although acupuncture is increasingly used as an adjunctive therapy for RIF patients, robust evidence supporting its efficacy in improving pregnancy outcomes is still lacking. This pilot study therefore aims to estimate effect sizes to inform sample size calculations for future definitive trials and to assess key feasibility parameters.

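### The secondary outcomes may be tested by Fisher's exact or Mann-Whitney tests after a normality pre-test, with outcomes multiply imputed; those tests give nothing for Rubin's rules to pool, and no secondary estimate with an interval is named

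*Protocol article*

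**What the plan says.** All the analysis text comes from the Statistical analysis section of the protocol article.

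- **Pre-test.** "Before conducting comparative analysis tests on all variables, a data normality test will be performed first". No outcome is exempted.
- **Clinical pregnancy.** The comparison is by "χ² or Fisher’s exact tests for dichotomous outcomes (clinical pregnancy rate").
- **Hormones** (β-hCG, LH, progesterone and estradiol, all measured 14 days after transfer according to Secondary outcomes). The comparison is by "independent samples t-tests or Mann-Whitney U tests for continuous variables (reproductive hormone levels").
- **Missing data.** "The intention-to-treat population will serve as the primary analysis set, with missing outcome data will be handled using multiple imputation" by chained equations, assuming missing at random. The sentence follows the secondary-outcome tests and covers outcome data in general.
- **Reporting.** For the primary GEE model only: "Results will be reported as odds ratios with 95% confidence intervals and P-values based on robust standard errors". No effect measure or interval is named for a secondary outcome.

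The Abstract says the study "aims to estimate effect sizes to inform sample size calculations for future definitive trials", and the Discussion repeats that focus. The Sample size section sets 100 participants, 50 per group.

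**The concern.** Multiple imputation produces several completed data sets. Rubin's rules turn these into one answer by averaging an estimate and combining its within-copy and between-copy variance. The secondary tests and the imputation are both stated choices in the same paragraph, and for two of the four tests they do not fit together.

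The pre-test adds a second difficulty. The mean difference behind a t-test and the rank comparison behind Mann-Whitney are different quantities. If a normality test chooses between them, what is compared for each hormone depends on the sample, may differ between the four hormones, and may differ between imputed copies of the same hormone.

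At stake is how useful the pilot is to whoever designs the next trial. The article says later trials should use more clinically meaningful endpoints. Of the outcomes measured here, clinical pregnancy is the closest to those, and for that purpose a P-value says far less than a difference with its interval.

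**Working it through.** The plan gives no figure of its own on this point, so there is none to reproduce. The check sets the named tests against what pooling needs, then works one example.

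**Step 1. What each named test supplies per imputed copy**

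| Outcome | Test | Estimate and SE? | Combining route |
|---|---|---|---|
| Clinical pregnancy | χ² | No, a statistic | D2 rule; gives a P-value, no effect size |
| Clinical pregnancy | Fisher's exact | No, a P-value | None under Rubin's rules |
| Hormones | t-test | Yes, mean difference and SE | Rubin's rules |
| Hormones | Mann-Whitney | No, a P-value as named | None under Rubin's rules |

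The mismatch is therefore confined to Fisher and Mann-Whitney.

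**Step 2. Worked example for clinical pregnancy**

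The data are assumed: 50 per arm, observed pregnancies 16/45 v 9/45, so 5 of 50 (10%) missing in each arm. The document states no missing rate. Missing values are imputed within arm from a Beta(s + 0.5, n − s + 0.5) posterior, with m = 20 copies.

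- *Fisher's exact.* The 20 P-values run from 0.027 to 0.387. There is no estimate and variance to average.
- *χ² by D2.* The mean χ² is 3.148, and r = (1 + 1/m) × var(√χ²) = 0.128. D2 = [3.148 − (21/19) × 0.128] / (1 + 0.128) = 2.66, P = 0.103. This is one answer, but not an effect size.
- *Risk difference by Rubin's rules.* The mean difference is 0.156, within-copy variance W = 0.00778 and between-copy variance B = 0.00099. T = W + (1 + 1/20)B = 0.00778 + 1.05 × 0.00099 = 0.00882, so SE = √0.00882 = 0.0939. The 95% CI is 0.156 ± 1.962 × 0.0939 = −0.028 to 0.340, P = 0.097. This is one answer, with the interval a later design needs.

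**Step 3. What the normality pre-test can apply to**

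Clinical pregnancy is yes/no, and so is implantation of each embryo in the primary model. A normality test says nothing about either. Among the outcomes it can act only on the four hormones. Each imputed copy holds different filled-in values, so a pre-test near its threshold can pass in one copy and fail in another. Nothing in the text says which test then applies.

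**Step 4. Whether one log-scale model would suit all four hormones**

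It would not suit β-hCG. At 14 days most women are expected not to be pregnant, so most values would lie near zero. Suppose 35% v 20% are pregnant, the pregnant geometric mean is 500, and all other values are set to a floor f (all assumed). The ratio of geometric means is then (500/f)^(0.35 − 0.20):

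- f = 0.1: 5000^0.15 = 3.6
- f = 1: 500^0.15 = 2.5
- f = 5: 100^0.15 = 2.0

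The answer depends on the floor, so β-hCG needs its own method.

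**The case against.** The strongest reply is that a condensed article may leave the number of imputations, the combining rule and the secondary effect measures to an analysis plan. The Randomization and blinding section foresees such a plan, final before the statistician is unblinded. This stands as far as it goes: the absence of a combining rule is not held against the document. It does not remove the point, because the article itself names the P-value-only tests, the pre-test and the imputation.

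Several stronger readings are tempting, and the document does not support them.

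- *A reader might infer that the secondary analyses cannot be finished once a value is missing.* The wording permits χ² or Fisher, and t-test or Mann-Whitney, so a combinable test is available for each outcome.
- *A reader might infer that tests will be picked with allocation known.* The blinding text says the analysis plan is finalised first.
- *A reader might take the spread of per-copy P-values as the size of the defect.* It is ordinary between-imputation variation. In the example above, the per-copy Wald P-values for the risk difference, the measure proposed here, run from 0.012 to 0.277. The difference is that the risk difference can be pooled.
- *A reader might infer that the trial yields no effect size.* The primary outcome has an odds ratio with a 95% CI, and Sample size ties the preliminary estimates to implantation rate.

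It is also fair to say that normality pre-testing is a common convention, and that a rank comparison is defensible for β-hCG. The objection here is to a data-driven choice, not to ranks as such.

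**Conclusion.** The point holds in a limited form and is minor. Fisher's exact and Mann-Whitney, as named, do not fit imputation that extends to the secondary outcomes. The normality pre-test is meaningless for yes/no outcomes and leaves the hormone comparison undetermined. No secondary estimate with an interval is named in a trial whose aim is estimation. The primary analysis is untouched.

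How much this matters depends on how many outcomes are missing, which the document does not state. With complete data the pooling problem disappears, while the pre-test and the lack of a named estimate remain. The worked figures rest on assumed counts and 10% missing and show the mechanism only. They are not a forecast for this trial.

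**What to change.** Change the secondary-outcome wording in Statistical analysis, before database lock:

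1. Delete the normality pre-test.
2. Report clinical pregnancy as a risk difference (or an odds ratio from a logistic model) with a 95% CI, pooled by Rubin's rules.
3. Report LH, progesterone and estradiol as a mean difference, or a ratio from a log-scale model, with a 95% CI pooled by Rubin's rules. Choose the scale for each hormone in advance.
4. Keep β-hCG out of the log-scale model. Fix one method for it in advance and, if its missing values are imputed, say how results are combined.

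The cost is wording only; no data collection or sample size changes. A log-scale ratio needs a line of explanation, and β-hCG will be reported differently from the other three hormones.
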